**Fig. 3 Fig3:**
[figure not shown]
Consort Flow Diagram depicting the SENATOR clinical trial organization

### Economic evaluation plan

The primary economic evaluation will present the cost-effectiveness of the SENATOR intervention and compare the costs with the primary endpoint of the SENATOR intervention against usual care. A cost-utility analysis (CUA) will also be undertaken to estimate the costs and utilities as reported as quality-adjusted life years (QALYs) over the 12-week follow-up period. The incremental cost-effectiveness ratio (ICER) will therefore present the cost per incremental ‘Quality Adjusted Life Year’ of SENATOR in relation to standard management.

Costs for calculation will include medication use, inpatient stay, further hospitalizations, hospital outpatient visits (including physiotherapist, OT), and community-based or health/social care visits. Resource use will be calculated according to the average unit cost of inpatient, outpatient and community visits across sites. In light of the intervention having no clear explicit cost/price, deployment costs of the SENATOR tool from an end-users’ perspective will be estimated by means of a brief user-survey.

The outcomes will be estimated as utilities, as reported from EQ-5D-3 L [18] eCRF data at baseline, day 14 or discharge, and 12-week follow up. The difference in QALY score between the two arms will be estimated using the “area under the curve” method.

The analysis will be undertaken from a payer perspective. Appropriate sensitivity and statistical analysis will be undertaken to test the uncertainty of the effect on the cost and QALY effect.

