### Data management

Although pragmatic and using a ‘real world’ approach to the dissemination of the SENATOR report and with a variable degree of engagement by the clinician, it has been necessary to develop and use a trial specific database to gather the inputs used by the SENATOR software in a standardized fashion from the different countries and to collect the trial outcome data which are collected to a far greater degree of precision and accuracy than is usual in clinical practise. To this end, data are entered electronically by the local site research staff into a cloud based database developed by Clininfo®. Data collected is pseudo-anonymized and includes baseline past medical history, current prescription medications and doses, routine blood biochemistry and haematology laboratory data, baseline ECG data, cognitive assessment using the Mini-Mental State Examination [16], functional assessment using the Barthel Index [17], and health related quality of life using the EQ-5D-5 L [18]. At day 14 post randomization or at discharge, whichever occurs first, the EQ-5D-5 L is repeated, the subjects medical conditions reviewed and medications recorded. The case records are reviewed to assess the number of SENATOR recommendations that have been adopted and to identify any potential endpoints as discussed below. At discharge arrangements are made with participants and/or their family for a 12 weeks (+/− 4 weeks) post hospital discharge follow-up call by the local site research staff. This is to enquire about healthcare utilization and any re-hospitalization since the index hospitalization, changes in medications and current health related quality of life.

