Acute dyspepsia/nausea/vomiting	Subjective symptoms of acute ‘indigestion’/‘upset stomach’ or acute abdominal pain or acute refusal to eat or acute heartburn/acid reflux or acute nausea/vomiting
Acute diarrhoea	New liquid stools reported by the patient or the nursing staff or new liquid stools detected by medical staff on physical examination or new liquid (non-solid) stools occurring more than 3 times in 24 h
Acute delirium	Confirmed by a reliable witness and the DSM-V criteria. Supported by a 4AT ≥ 4 and/or MMSE < 23/30
Symptomatic hypoglycaemia	Symptoms with a blood glucose of < 3.5 mmol/L or < 63 mg/dl.
Unspecified adverse event	For ADEs not specified above e.g. acute liver failure, anaphylaxis

Exploratory Endpoints include all-cause mortality during index hospitalization; re-hospitalisation, composite healthcare utilization, and health related quality of life at 12 weeks post-discharge follow-up; and utilization of non-pharmacological interventions.

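### The QALY difference between arms is specified as an area-under-the-curve estimate with no covariate named; regression on baseline utility and the randomisation strata would be more precise at no extra data cost

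*Protocol article*

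**What the plan says.** The Economic evaluation plan adds a cost-utility analysis to the primary economic evaluation, which is based on the ADR endpoint. It takes utilities from "eCRF data at baseline, day 14 or discharge, and 12-week follow up" and reports "quality-adjusted life years (QALYs) over the 12-week follow-up period". The estimation sentence is: "The difference in QALY score between the two arms will be estimated using the" area-under-the-curve method. No covariate is named. The section closes by promising appropriate sensitivity and statistical analysis of the uncertainty in the cost and QALY effects, without saying what that is.

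The Data management section confirms that baseline data include "health related quality of life using the EQ-5D-5 L", and says of the second measurement: "At day 14 post randomization or at discharge, whichever occurs first, the EQ-5D-5 L is repeated". The third comes from a follow-up call 12 weeks (plus or minus 4) after discharge.

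By contrast, the Statistical methods section does name covariates for the primary endpoint: site and medical versus surgical admission. It says secondary endpoints will be handled similarly. The QALY is not among the listed secondary endpoints, so that sentence does not reach it.

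**The concern.** A QALY built from three utilities contains the baseline utility and is also correlated with it through the later two. If the arms differ at baseline by chance, a difference in mean areas takes that difference over into the incremental QALY, which is the denominator of the cost per QALY. Over roughly 14 weeks any QALY difference is small, so a shift of a few thousandths is not negligible. Regression on baseline utility removes the carry-over and narrows the interval. Baseline EQ-5D and the strata are part of the data already planned.

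**Working it through.** **The plan's own figure.** The article gives no figure for QALYs. It gives 900 per arm for 90% power on the primary endpoint, which I use as the sample size. With an 18% control rate and odds ratio 0.65, the intervention odds are 0.65 × 0.18/0.82 = 0.1427, a rate of 12.49%. The pooled-variance formula for two proportions gives 892 per arm for 90% power, and 90.3% power at 900. The stated figure reproduces.

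**Inputs from the article.** 900 per arm; 1:1 allocation; utilities at baseline, at day 14 or discharge, and 12 weeks after discharge.

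**Assumptions not in the article.** Utility SD 0.25 at each visit; the same correlation ρ between any two visits, from 0.3 to 0.7; complete data; visits at days 0, 14 and 98. A second visit at day 3 or 7 (last visit 84 days later) is used as a variation.

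**1. Weights.** By the trapezoid rule, the three utilities receive weights of 14/2 = 7, 98/2 = 49 and 84/2 = 42 days, each divided by 365.25 for years. The direct share of baseline is 7/98 = 7.1%. It is 3.5/91 = 3.8% with discharge at day 7 and 1.5/87 = 1.7% at day 3. It would reach 7/70 = 10% only if follow-up came at 8 weeks after a day-14 visit.

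**2. Correlation of QALY with baseline, ρ = 0.5.**
- Covariance with baseline, in units of SD² × days: 7 + 0.5 × (49 + 42) = 52.5.
- Variance of the area: 7² + 49² + 42² + 2 × 0.5 × (7×49 + 7×42 + 49×42) = 4,214 + 2,695 = 6,909; square root 83.1.
- r = 52.5/83.1 = 0.63, so r² = 0.40.

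**3. Precision.** The unadjusted SE is 0.25 × 83.1 × √(2/900)/365.25 = 0.0027 QALY. Adjustment multiplies it by √(1 − r²) = 0.775, giving 0.0021. The equivalent sample-size factor is 1/(1 − r²).

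| ρ | r | Variance cut, day 14 | Sample-size factor, day 14 | Variance cut, day 3 |
|---|---|---|---|---|
| 0.3 | 0.45 | 20% | 1.25 | 15% |
| 0.5 | 0.63 | 40% | 1.66 | 35% |
| 0.7 | 0.79 | 63% | 2.67 | 59% |

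(The r column is for day 14.) These ratios do not depend on the SD. They cover baseline utility only; any further gain from the strata is not counted.

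**4. Carry-over of a chance imbalance.** The SE of the baseline difference is 0.25 × √(2/900) = 0.0118, so a difference of 0.02 is 1.7 SE (two-sided probability about 9%). The slope of QALY on baseline at ρ = 0.5 is 52.5/365.25 = 0.144. The expected shift is 0.02 × 0.144 = 0.0029 QALY, about one unadjusted SE. Only 0.02 × 7/365.25 = 0.0004 of that, about 13%, is the direct part; the rest comes through correlation with the later utilities.

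**5. Simulation.** Three thousand simulated trials (SD 0.30, ρ = 0.5, day 14) gave both estimators an average of about zero. The SD of the estimate was 0.0032 unadjusted and 0.0025 adjusted. The unadjusted difference correlated 0.63 with the baseline imbalance, the adjusted one −0.01.

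**The case against.** The strongest objection is that area under the curve is how a patient's QALY is built, and the article does not say the arm contrast is unadjusted. A regression could sit in a fuller plan that is not shown. This stands as far as wording goes: a reader might infer that the article commits to a plain difference in means, and it does not say so. What remains is that the sentence gives the method for the between-arm difference, and the article names covariates for its primary endpoint. The closing promise concerns uncertainty and supplies no adjustment.

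A reader might also infer bias. Individual stratified randomisation rules that out on average; the carry-over is sampling error that the unadjusted interval already reflects. The loss is of precision and of robustness to the imbalance actually realised.

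A third tempting reading is that the trouble lies in baseline being part of the area. That is the minor route, as step 4 shows.

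Finally, a reader might extend the point to the exploratory endpoint listed as "re-hospitalisation, composite healthcare utilization, and health related quality of life at 12 weeks post-discharge follow-up". That list names outcomes and a time point and fixes no analysis. A follow-up value is also what a baseline-adjusted model would take as its outcome. No fault is shown there.

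The size rests on assumed SD, correlation and complete data; deaths and missing follow-up are ignored. Fixing the second visit at day 14 favours adjustment somewhat. The article plans no hypothesis test on QALYs, so the gain is given here as variance and not as power.

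**Conclusion.** The point holds as a free improvement to a secondary economic analysis. As written, the QALY difference is specified without baseline or stratum adjustment. Under the stated assumptions, adjusting for baseline utility would cut its variance by about 20% to 63% with a second visit at day 14, and by about 15% to 59% with discharge at day 3. At a correlation of 0.5, a baseline difference of 0.02 would otherwise move the incremental QALY by about 0.0029, roughly one SE. The direction of the conclusion does not depend on the assumed values, provided baseline utility correlates with later utility; its size does. The primary endpoint, its model and the sample size are untouched.

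**What to change.** In the Economic evaluation plan, keep the area-under-the-curve QALY for each patient. State that the difference between arms will be estimated by regressing that QALY on arm, baseline EQ-5D utility, site and medical/surgical stratum. State also that this adjusted estimate is the one used in the cost per QALY and in its uncertainty analysis. The cost is one or two sentences and no new data. Fixing this before outcome data are examined also removes a later choice between adjusted and unadjusted results.

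The same edit should settle the instrument: Data management names the five-level EQ-5D and the Economic evaluation plan the three-level version for the same assessments. That is a separate inconsistency, but the baseline covariate and the QALY must come from one instrument and value set.

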## Discussion

With a progressive global shortage of specialist geriatricians to treat the rapidly growing frailer multi-morbid older population, pragmatic cost-effective strategies to improve pharmacotherapy for older adults are urgently needed. The majority of drug prescriptions for older multi-morbid people currently and in the future will emanate from clinicians who are neither specialist geriatricians nor clinical pharmacologists. Strategies to optimise the pharmacotherapy of older multi-morbid people and simultaneously minimize drug-related harm must be devised and tested. Previous studies have shown that the implementation of medication reconciliation [21] and comprehensive geriatric assessment [22] reduce inappropriate prescribing and potentially ADRs, but both these approaches are time consuming, expensive and require experienced clinical staff. The SENATOR software has the capability of highlighting the most common potentially inappropriate prescriptions to a non-specialist clinician in an efficient manner and in so doing prompt alterations which will reduce risks of incident ADRs. If successful this will result in older patients suffering fewer adverse medication-related outcomes with associated economic benefits.

Prior to finalizing the trial protocol we conducted a non-interventional feasibility study at the same sites that are participating in the trial [23]. The feasibility study highlighted several challenges that led us to modify our initial trial design and our approach to the assessment of ADRs in the current trial.

We had initially proposed a cluster randomized trial adjusting for difference in baseline ADR risk using an ADR prediction tool such as the previously validated Gerontonet ADR Risk Scale [6]. This approach had the specific advantage of limiting contamination between the intervention and control arm, especially if it transpired that the same investigator was simultaneously attending a subject in both arms of the trial. However, in our feasibility study we discovered a very large degree of heterogeneity in ADR rates between different sites and between specialities within individual sites. Some of this heterogeneity may have resulted from initial limited standardization of our ADR reporting and adjudication processes and from sampling variability given the limited sizes of individual samples as well as real substantive differences between sites. Furthermore, we found that within our population the ADR predictions tools were inadequate for correcting for the between-cluster variability in baseline ADR risk. This made it impossible to exclude the possibility that any observed differences in the proposed trial might not simply be the consequence of an unequal distribution of baseline ADR risks across sites. We therefore adopted an individual level randomization, accepting that a degree of cross arm contamination might dilute the perceived effect size. However, even in a cluster design this effect is not fully prevented because junior medical staff routinely migrate between various specialities within a hospital and senior clinicians typically cross cover other specialist services at weekends and when working on-call outside of regular daytime hours.

The assessment of ADRs gives rise to several methodological complexities that have not previously been widely discussed in the literature. It is necessary to distinguish between prevalent (pre-dating the hospitalization and on occasion necessitating it) and incident ADRs, which occur during the index hospital stay. These are likely to differ in their characteristics, risk factors and consequences, making the distinction particularly relevant for ADR risk prediction tools. From the SENATOR trial viewpoint, it is necessary to exclude ADRs occurring prior to randomization; therefore outcomes in this trial will only include in-hospital incident ADRs that occur post randomization, but we also take account of whether identification and response to prevalent ADRs is influenced by study intervention.

The feasibility study highlighted the difficulty in reliably separating prolonged or repeated occurrences of the same ADR into separate discrete events in a reproducible fashion. This would necessitate defining a minimal interval between events and requires more detailed information on the timing of events than is usually present in clinical records or at least amenable to retrospective assessment. We therefore conceptualized ADRs as processes which are predisposed by one or more medications. This uses a patient-specific rather than a medication-specific perspective, therefore an ADR with two different potential implicated medications at different times is still considered a single potential endpoint. This potential loss of precision in defining ADRs is necessary for reproducibility and avoidance of an unduly subjective determination of the number of discrete episodes.

We adopted a retrospective approach to ADR assessment for two reasons. Firstly, real time assessment could potentially influence attending clinician or patient behaviour independently of the intervention. Secondly, there is the need to avoid situations where the site researcher identifies a potentially dangerous inappropriate prescribing in real time, leading to an ethical dilemma of whether or not to alert the attending clinical staff, thereby potentially distorting trial data. While a retrospective assessment may result in some ADRs not being clearly identified, our contention is that an adverse event that does not leave any evidence in the medical notes, nursing notes or elsewhere in the case records in the highly monitored hospital environment is more likely to be trivial in nature.

In keeping with the open label design that is unavoidable in a trial of a decision support tool and in view of the somewhat subjective nature of ADR ascertainment, it is necessary to use a detailed process to allow for blinded potential end-point adjudication. We optimized the function of this process by the use of an algorithm that varies the number of required potential end-point reviews depending on the degree of concordance between blinded reviewers and the strength of the initial reviewers’ assessment. We have also considered carefully the definitions used in our outcomes. Thus, the distinction between ‘certain’ and ‘probable’ ADR is less relevant as both are primary endpoints in contrast to the distinction between ‘possible’ and ‘probable’ ADR and between ‘possible’ and ‘unlikely’ ADR which have more influence on the secondary outcomes.

SENATOR is a complex clinical trial with many challenges. For this trial to succeed, attending clinicians in the intervention arm need to implement the recommendations of the SENATOR report. To date, adherence with software-generated prescribing advice in other studies has been highly variable [24]. In addition, ADRs need to be recorded and adjudicated in a comprehensive and unbiased fashion. SENATOR is the first multi-national randomized trial in which a prescribing optimization software specially designed to minimize ADRs and potential prescribing omissions will be tested on a large scale. If the SENATOR trial shows the software to be effective for minimizing ADRs and their consequences, there is the potential for routine prescribing optimization for large numbers of multi-morbid older people that is software-driven. A critical question that this trial will address is the extent to which the prescribing advice provided in the software-generated SENATOR report will be considered appropriate by busy clinicians and applied accordingly to their patients’ prescriptions in the acute hospital setting.

## Abbreviations

ADR: Adverse Drug Reaction
ONTOP: Optimal evidence-based Non-drug Therapies in Older People
SENATOR: Software ENgine for the Assessment and optimisation of drug and non-drug Therapy in Older peRsons
START: Screening Tool to Alert doctors to the Right Treatment
STOPP: Screening Tool of Older Persons’ Prescriptions
